## Abstract

**Background:**

Major depression can be a serious and debilitating condition. For some patients in a treatment resistant depressive episode, electroconvulsive treatment (ECT) is the only treatment that is effective. Although ECT has shown efficacy in randomized controlled trials, the treatment is still controversial and stigmatized. This can in part be attributed to our lack of knowledge of the mechanisms of action. Some reports also suggest potential harmful effects of ECT treatment and memory related side effects have been documented.

**Methods/design:**

The present study will apply state of the art radiology through advanced magnetic resonance imaging (MRI) techniques to investigate structural and functional brain effects of ECT. As a multi-disciplinary collaboration, imaging findings will be correlated to psychiatric response parameters, neuropsychological functioning as well as neurochemical and genetic biomarkers that can elucidate the underlying mechanisms. The aim is to document both treatment effects and potential harmful effects of ECT.

Sample: n = 40 patients in a major depressive episode (bipolar and major depressive disorder). Two control groups with n = 15 in each group: age and gender matched healthy volunteers not receiving ECT and patients undergoing electrical cardioversion (ECV) for atrial fibrillation (AF). Observation time: six months.

**Discussion:**

The study will contribute to our understanding of the pathophysiology of major depression as well as mechanisms of action for the most effective treatment for the disorder; ECT.

## Background

### Bipolar and major depressive disorder

Bipolar disorder and major depressive disorder (MDD) are mental disorders with a 12-month prevalence in the EU of about 1 and 7%, respectively [1]. They are associated with a reduced quality of life, an increased mortality risk, and are a major cause of inability to work [2,3].

The management of depression includes psychosocial treatment approaches, pharmacotherapy and, for the most severe and treatment resistant patients, electroconvulsive treatment (ECT).

### Electroconvulsive treatment

The idea that convulsions could treat mental illness can be traced to the 16^th^ century, when camphor oil was used to induce convulsions. Seizure-induction by application of electrical current to the human brain was introduced by the Italians Cerletti and Bini in 1938 [4]. Since its introduction, ECT has been applied to various psychiatric and some somatic conditions. Modern ECT has fewer indications and has been developed with the aim to reduce side effects [5].

For some patients in a treatment resistant depressive episode, ECT is the only treatment that is effective. ECT is generally considered to be safe and has shown efficacy in randomized controlled trials [6]. A recent randomized controlled trial found ECT to be more effective than pharmacological treatment for treatment-resistant bipolar depression [7]. However, the treatment is still controversial and stigmatized [8]. This can in part be attributed to our lack of knowledge, since the mechanisms of action is still largely unknown.

Some have compared ECT to lobotomy [9] or hypothesize that ECT affects the brain in a manner similar to severe stress or trauma [10]. Others regard it as a safe treatment that is underused [11], and a systematic review found no persistent cognitive deficits after ECT [12]. A recent randomized controlled trial of right unilateral ECT in treatment resistant depression found no changes in general neurocognitive function, but reduced autobiographical memory consistency after ECT [13]. This finding is in line with subjective patient reports [14], and further research is required.

The NICE guidelines states: “Consider ECT for acute treatment of severe depression that is life-threatening and when a rapid response is required, or when other treatments have failed” [15]. This is in line with the Norwegian national guidelines that recommend ECT in major depression when other treatments have been ineffective (Evidence level A, [16]), and there has been an increase in its use in recent years [17].

Increased knowledge gained through thorough scientific investigations can reduce stigmata and inform patients and health care providers to make appropriate use of ECT. Better understanding of ECT and its mechanisms of action may help patients to cope with side effects and contribute to the development of new treatment options.

### Possible mechanisms of action of ECT

More than one hundred theories have been suggested for the effects of ECT [5]. Although changes to brain structure in major depression have been confirmed by several meta-analysis [18-20] and ECT-induced structural and functional changes have been characterized (for recent reviews see [21-23]) we still lack a unifying theory for its mechanisms of action. The project will focus on three suggested effects of ECT, each reflecting proposed pathophysiological changes and mechanisms of action, see below. As a multidisciplinary study, results from the neuroradiological measures can be correlated to biomarkers in blood and behavioral parameters; e.g. improvement/remission after ECT should be correlated to improved performance on neuropsychological testing. For dichotic listening, improved scores in the forced left condition would indicate better cognitive control.

### Hippocampal volume

The human nervous system adapts to challenges. It can be changed by learning as well as by pathological conditions, such as psychiatric disorders. One structure that has been studied in large detail in this regard is the hippocampus; a structure that is important for learning and memory. Hippocampal volumes are *reduced* in major depressive disorder [19,24,25] and in a number of other psychiatric and somatic disorders (reviewed in [26]). The volume reduction of the hippocampus has been associated with duration of untreated depression [27]. On the other hand, *increased* hippocampal volumes can occur after extensive learning, e.g. studying to become one of London’s taxi drivers [28,29]. The *increase* in hippocampal volumes may be related to neurogenesis, which has been shown to occur in animal models [30,31]. In primates, the proliferation of granular cells in the dentate gyrus of the hippocampus was shown to be reduced by stress [30]. Seizures induce neurogenesis in rodents [32], and animal models have shown electroconvulsive seizures to have effects on neurotransmitters, gene expression, growth factors (such as Brain derived neurotrophic factor - BDNF, Vascular endothelial growth factor - VEGF, Fibroblast Growth Factor - FGF) and neuropeptides (such as neuropeptide Y - NPY, Thyrotropin-releasing hormone - TRH, VGF) and lead to synaptic remodeling and cellular proliferation (reviewed in [33]). Research from animal models also indicate that electroconvulsive shocks can reverse the effect of cortisol and even cause an increase of hippocampal volumes (reviewed in [5]).

Increased levels of BDNF has been reported following ECT [34], and BDNF has been suggested as a potential biomarker for depression [35]. Neurogenesis has been shown to occur in the dentate gyrus of the hippocampus in adult humans [36], and ECT-induced neuroplasticity is gaining more focus as a framework for understanding the effects of ECT [23]. A few studies of humans have reported increased hippocampal volumes and/or other structural changes following ECT [37-41]. Nordanskog et al. [39,41] performed manual segmentation without complete blinding of the MRI time point that was traced (before or after ECT), introducing a potential observer bias. Dukart et al. [38] used voxel-based morphometry, while Tendolkar et al. [40] and Abbot et al. [37] both used FreeSurfer [42] for volumetric segmentation and analysis. Compared with these studies we will recruit more patients, use state of the art automatic segmentation procedures, and radiology readers will be blinded to study group and the time point of MRI scans. In addition, by applying multimodal imaging, structural changes can be assessed with respect to changes in diffusion properties, susceptibility weighted imaging (SWI) and fluid attenuated inversion recovery (FLAIR) imaging. Our design will allow longitudinal tracking of brain changes; 1-2 hours after the first ECT, after treatment completion and at 6 months follow up.

### Gamma-Aminobutyric acid (GABA) and connectivity

ECT has anticonvulsive effects and is sometimes used in the treatment of status epilepticus [43]. One hypothesis suggests that the magnitude of increase in seizure threshold, induced by ECT, is important for the antidepressant efficacy [44]. Drugs that enhance GABAergic neurotransmission are known for their anticonvulsant effect, and the role of amino acid neurotransmission systems, particularly reduced function of GABAergic neurotransmission has been increasingly appreciated in major depression (for reviews, see [45,46]). Tiagabine, a selective GABA reuptake inhibitor was shown to be effective in treatment of depression with anxiety [47]. A post mortem study of gene expression in elderly depressed patients found alterations in GABA and glutamate pathways markers indicating diminished activity in the anterior cingulate cortex (ACC) [48]. A recent meta-analysis suggested increased resting-state activity in the rostral ACC as a biomarker for treatment response in major depression, and a shift from GABA- to glutamate-mediated modulation was suggested [49].

Interestingly, one early study found increased concentrations of cortical GABA after ECT in depressed patients by use of proton magnetic resonance spectroscopy (^1^H-MRS) [50], however this finding has to our knowledge not been reproduced by other groups.

It has recently been suggested that “hyperconnectivity” in networks involved in mood regulation can be reduced after a course of ECT [51,52]. This finding may seem contrary to findings of increased fractional anisotropy (FA) in frontal limbic projections after a course of ECT [53,54]. FA is often regarded as a measure of white matter tract integrity and increased axonal integrity may seem contra-intuitive if one expects reduced connectivity after ECT. Possible explanations could be that the projections that are “enhanced” by ECT are GABAergic, or that improved integrity of certain projections may lead to more coordinated electrical activity in these projections, which overall is detected as “reduced connectivity”.

Our project will encompass measures of neurotransmitters (GABA and glutamate by ^1^H-MRS) and diffusion parameters (e.g. fractional anisotropy, mean diffusivity and separation of restricted and hindered water by Restriction Spectrum Imaging, RSI [55]), enabling longitudinal investigations of GABA- and glutamate levels as well as white matter properties in the same patients.

### ECT and harmful effects

ECT has been a controversial treatment from its introduction. The most important side effects are related to memory impairments [6] and it is recommended that the patients’ cognitive functioning is monitored both during and after treatment [16]. A recent randomized controlled trial in treatment-resistant bipolar depression found reduced autobiographic memory consistency after ECT but no deterioration of general neurocognitive function [13]. Structural damage to the human brain has to our knowledge, never been documented to be caused by ECT. Case studies with rare complications, such as subdural hematoma, have been published [56], however a study using cerebral Computer Tomography in 40 patients before and after ECT detected no changes caused by ECT, even with convulsions lasting several minutes [57]. Both conventional MRI and diffusion weighted imaging (DWI; a sequence that is sensitive to edema) have failed to find structural damage [58]. However, changes on DWI have been shown for patients after status epilepticus [59]. If brain injury occurs as a consequence of ECT, one may expect to find micro hemorrhages. SWI is extremely sensitive to hemorrhages, and is routinely used in imaging of stroke [60]. However, SWI, as an indicator of microvascular dis-integrity, has to our knowledge never been applied after ECT. In addition, by using ^1^H-MRS we will measure N-acetylaspartate (NAA), which is primarily localized in neurons and considered a marker for neuronal integrity [61].

Our project will use high field strength, state of the art MRI and combine RSI, SWI and ^1^H-MRS which should enable detection of more subtle post-ECT effects.

### Hypotheses and aims

Based on the above discussions, the following main hypotheses define the outline and aims of this project:Hippocampal volumes increase after ECT treatment. A) Specifically there is increased volume of the dentate gyrus, which would suggest that the increase is caused by neurogenesis. B) Changes in hippocampal structure correlate with treatment response, neurocognitive measures and increased concentrations of neurotrophic factors in blood samples.ECT causes increased levels of the neurotransmitter GABA and changes the glutamate/GABA balance. A) GABA concentrations correlate with treatment response. B) Genes regulating GABA synthesis and cycling are up-regulated or activated. C) A subset of cortical projections is strengthened; a possible mechanism causing reduced connectivity in frontal areas.ECT does not cause measurable signs of harmful effects to the brain. A) No changes are detected on microvascular (SWI) and microstructural (RSI) imaging. NAA (measurend in the ACC) is unaffected. B) Possible immediate post-ECT effects, e.g. edema, that is detectable by diffusion weighted imaging, are reversible.

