### Power analysis

Only one study has measured GABA changes after ECT by MRS in humans, and found an increase from 0.85 (SD = 0.34) to 1.51 (SD = 048) mmol/kg brain tissue, N = 8 [50]. Using a mean difference of 0.6 and a SD of 0.5, α = 0.05 and power of 0.8 the total sample size needed would be 8 (calculated using G*Power 3.1.3, paired t-test, two-tailed).

For analysis of hippocampal volumes, data from Nordanskog et al. [41] were used. For the right hippocampus the mean difference in volumes after a course of ECT was 133 μL with a SD of 123 μL, similar analysis as above indicates that the sample size needs to be at least 9.

We found no studies on SWI and DWI imaging that could be used to estimate power of the suggested study protocol. Based on the analysis above, a total of 10 patients is a minimum. Due to wide inclusion criteria, expected heterogeneity of the sample population and in order to increase the robustness we intend to include 40 patients.

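### Hypothesis 1A takes increased dentate gyrus volume as suggesting neurogenesis but names no comparator region, so uniform hippocampal enlargement would satisfy it as well

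*Protocol article*

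**What the plan says.** The section Hypotheses and aims opens with the parent hypothesis, "Hippocampal volumes increase after ECT treatment", and continues with 1A: "Specifically there is increased volume of the dentate gyrus, which would suggest that the increase is caused by neurogenesis". The reason for choosing this subfield is in the section Hippocampal volume: "Neurogenesis has been shown to occur in the dentate gyrus of the hippocampus in adult humans".

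No section compares the dentate gyrus with other subfields or with the rest of the hippocampus. Image processing and analysis names the software for structural data and no contrast for 1A.

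Material that bears on the interpretation appears elsewhere. Hippocampal volume says that structural change can be viewed against diffusion, SWI and FLAIR findings, and that brain changes will be tracked "1-2 hours after the first ECT, after treatment completion and at 6 months follow up". Hypothesis 1B looks for correlation with treatment response, neurocognitive measures and neurotrophic factors in blood. Hypothesis 3B states: "Possible immediate post-ECT effects, e.g. edema, that is detectable by diffusion weighted imaging, are reversible". None of these is made part of the inference in 1A.

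**The concern.** The inference runs from a larger dentate gyrus to neurogenesis as the cause of hippocampal growth. To carry weight, the finding should be more likely under neurogenesis than under rival explanations. A dentate increase taken alone is not. If hypothesis 1 is true and growth is spread evenly, the dentate gyrus grows with everything else, whatever the cause. The protocol itself mentions other processes: synaptic remodeling in animal models (Hippocampal volume) and edema as a possible immediate effect (hypothesis 3B).

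At stake is the mechanistic part of hypothesis 1. Read at face value, 1A could be reported as supported in a study where the dentate gyrus behaved no differently from the rest of the hippocampus.

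**Working it through.** **Inputs from the protocol article (Power analysis; Patients)**
- Right hippocampus: "For the right hippocampus the mean difference in volumes after a course of ECT was 133" μL, "with a SD of 123" μL.
- Two-tailed paired t-test, α = 0.05, power 0.8.
- Planned sample 40, of whom 32 follow the protocol as described.

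**Assumptions (not in the article)**
- Every subfield grows by the same percentage, so there is no dentate-specific effect.
- 1A is tested as dentate change against zero with a paired t-test. The article uses that test only in its sample-size calculations for GABA and whole-hippocampus volume.
- Subfield measurement noise is varied over a range, because the article gives no subfield volume or SD.

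**Step 1: reproduce the plan's own figures.** Standardized change dz = mean / SD; exact power from the noncentral t distribution with n − 1 degrees of freedom and noncentrality dz × √n.
- GABA: dz = 0.6/0.5 = 1.2. Power is 0.754 at n = 7 and 0.828 at n = 8, so n = 8, as stated.
- Hippocampus: dz = 133/123 = 1.081. Power is 0.747 at n = 8 and 0.810 at n = 9, so n = 9, as stated.

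The power calculation is not in error.

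**Step 2: carry the hippocampal effect to the dentate gyrus.** Under uniform growth, the dentate change is a fixed share of the hippocampal change. Mean and SD shrink by the same factor, so dz stays at 1.081 if measurement is equally precise. Extra dentate noise with SD r times the SD of the true dentate change gives dz = 1.081/√(1 + r²). Reducing dz to a fraction f of 1.081 corresponds to r = √(1/f² − 1).

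**Step 3: probability of finding a dentate increase when there is no dentate-specific effect**

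| f | r | dz | n = 32 | n = 40 |
|---|---|---|---|---|
| 1 | 0 | 1.081 | >0.999 | >0.999 |
| 0.75 | 0.88 | 0.811 | 0.99 | 0.999 |
| 0.5 | 1.73 | 0.541 | 0.84 | 0.92 |
| 0.4 | 2.29 | 0.43 | 0.66 | 0.76 |

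Heavier noise lowers the figure further: at f = 0.33 it is 0.50 for n = 32 and 0.60 for n = 40.

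**Step 4: compare with a contrast.** In simulation (20,000 runs per setting) of the same uniform-growth scenario, with r = 1 and r = 2, dentate change against zero was significantly positive in 0.997 and 0.85 of runs at n = 40. Percentage change in the dentate gyrus minus percentage change in the rest of the hippocampus was significantly positive in 0.0245 and 0.0256. That is the nominal 2.5% in one tail of a two-sided 0.05 test. The simulation put the extra noise on the dentate gyrus only.

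**The case against.** The strongest reply is that 1A is a hedged hypothesis and not a decision rule. It says only that the finding would suggest neurogenesis, and the word *specifically* can be read as saying that the growth is localized in the dentate gyrus. The article prescribes no test for 1A, and an analysis plan that is not shown may define a contrast. All of this stands, and it limits the point. What remains is that the only evidence named is an increase in dentate volume; the localized reading is not put into the criterion.

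Stronger readings are tempting, but the document does not support them:
- A reader might infer that neurogenesis will be declared confirmed whenever hypothesis 1 holds. No such rule is written, and the test against zero is an assumption made here.
- A reader might infer that the study cannot separate the competing explanations. It plans diffusion, FLAIR, a scan 1–2 hours after the first ECT, and blood neurotrophic factors, all of which can help; 1A simply does not draw on them.
- A reader might take edema as the likely cause of growth at visit 4. Hypothesis 3B treats edema as immediate and reversible, whereas visit 4 is 7–14 days after the last ECT. Nothing in the article says that edema would be uniform across subfields.
- A reader might argue that any increase seen at 1–2 hours cannot be neurogenesis. The article gives no source for that.

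**Conclusion.** The point holds in a limited form. As worded, 1A does not discriminate: an increase in dentate volume is what hypothesis 1 alone would predict under uniform enlargement. This is a weakness in a stated criterion, separate from any detail left to an analysis plan.

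The size, about 0.76 to over 0.99 at 40 patients, is conditional on uniform growth at the planning effect, on a test against zero, and on assumed noise with f between 0.4 and 1. It illustrates how little a dentate increase says about cause; it does not measure an error in a planned analysis. The sample size is unaffected. The change is worth making because mechanism of action is a stated aim of the study and the remedy is small.

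**What to change.** Restate 1A as a greater proportional change in the dentate gyrus than in the rest of the hippocampus, tested as a region-by-time contrast from visit 2 (before the first ECT) to visit 4 (7–14 days after the last). Word a positive result as consistent with neurogenesis.

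Report the same contrast at visit 3 (1–2 hours after the first ECT), and the planned diffusion and FLAIR changes, with estimates and confidence intervals as supporting evidence. Do not make them pass/fail conditions: requiring no early excess or no edema signal would treat a non-significant result as proof of absence.

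The cost is one contrast and a reworded sentence, on scans already planned. The contrast will have less power than a test against zero; how much less cannot be computed without subfield variances, which the article does not give. A dentate excess would still leave other local processes open, so it would not prove neurogenesis.

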### Methods and design

The study is prospective and observational, and all patients will receive the standard ECT treatment, as it is provided at the ECT-department at the Haukeland University Hospital.

A flow chart of the study design is shown in Figure 1, and details on study measures and variables are listed in Table 1.

**Figure 1 Fig1:**
[figure not shown]
Flow Chart of Study Design.

**Table 1 Tab1:** **Variable overview**

	Study visit	1	2	3	4	5
	Time point test	<7 d of first ECT	1– 2 h before first ECT	1– 2 h after first ECT	7 – 14 d after last ECT	6 mo after ECT-series
	Informed consent	X				
Diagnostic interview	MINI plus	X				
Clinical assessment	Clinical examination	X				
	Illness history, previous episodes and ECT-treatment	X				
	Current and concomitant medication	X			X	X
Symptom severity	MADRS	X			X	X
	CGI	X			X	X
Relapse	Interview					X
Overall cognitive function	MMS	X			X	X
Neuropsychological assessment	WASI	X				X
	CVLT-II, Rey, Digit span from WASI-R, WCST, D-kefs: Color-Word interference test, Word fluency, Tower, TMT, CPT, Digit symbol WAIS-R, Pegboard	X			X	X
Autobiographical memory	AMI-SF	X			X	X
Everyday memory	EMQ	X			X	X
Cognitive control	Dichotic listening	X			X	X
Blood samples	Full blood, EDTA and PAX-gen for biobank		X^1)^	X^1)^	X^1)^	X^2)^
Radiology	MRI caput; T1 FSPGR, T2 CUBE FLAIR, RSI, SWI, MRS, MEGAPRESS		X	X	X	X

^1)^Before MRI.

^2)^Before and after MRI.

Relevant patients with depression are addressed in order to establish whether they are willing to be screened for the study. The patients must be assigned a patient number and sign the consent form after receiving oral and written information about the study prior to undergoing any study procedures.

